### Study timeline

The study timeline is depicted in Table 1. See also the checklist enclosed in Additional file 2.

**Table 1 Tab1:** A TAPER-S study timeline

Screening and Randomization	
V0 – Days -3 to -1	
Signed and dated Informed Consent obtained prior to start any procedure scheduled for the study	
Verification and confirmation of the inclusion/exclusion criteria	
Randomization	
Demographics, medical history	
Physical Examination	
Vital Signs (BP, HR)	
NYHA Class definition	
Pregnancy Test (serum test or urine test as per decision of the clinician)	
Full Blood Count, Chemistry and Coagulation Tests	
ECG	
Echocardiography, if not performed within the last year from the Informed Consent signature	
Chest X-Ray	
VASP and VerifyNow Test	
Dyspnea Evaluation	
Drug Dispensing	
Drug Accountability	
Concomitant Medications	
Adverse Events	
Index PCI	
V1 – Day 0	
Verification and confirmation of the inclusion/exclusion criteria	
Vital Signs (BP, HR)	
ECG	
Ischemic Preconditioning	
Quantification of coronary microvascular resistance	
VASP and VerifyNow Test	
VAS Scale Evaluation	
Dyspnea Evaluation	
Drug Dispensing	
Drug Accountability	
Concomitant Medications	
Adverse Events	
Follow-up	
V2 – Day 1	
Physical Examination	
Vital Signs (BP, HR)	
ECG	
VASP and VerifyNow Test	
Dyspnea Evaluation	
Drug Dispensing	
Drug Accountability	
Concomitant Medications	
Adverse Events	
Pre-discharge Visit	
V3 – Day 2	
Physical Examination	
Vital Signs (BP, HR)	
Dyspnea Evaluation	
Drug Dispensing	
Drug Accountability	
Concomitant Medications	
Adverse Events	
Discharge/End of Study Visit	
V4 – Day 3 to Day 5	
Physical Examination	
Vital Signs (BP, HR)	
ECG	
Full Blood Count, Chemistry and Coagulation Tests	
Dyspnea Evaluation	
Drug Dispensing	
Drug Accountability	
Concomitant Medications	
Adverse Events	

### Assessments description

#### Dyspnea evaluation

The sensation of dyspnea will be reported by patients using the modified Borg scale; the scale is scored from 1 (no sensation of dyspnea) to 10 (maximum sensation of dyspnea) [39].

#### Assessment of platelet reactivity

We will perform platelet VASP (vasodilator-stimulated phosphoprotein) and VerifyNow test. The VASP test specifically assesses the inhibition of platelet reactivity index (PRI) linked to P_2_Y_12_ ADP receptor inhibition. The VASP test is a flow cytometry-based method that uses a phosphorylation-specific antibody and measures the PRI, expressed as a percentage and defined as the difference in VASP fluorescence intensity between resting (+PGE1, prostaglandin E1) and activated (+ADP) platelets. VASP phosphorylation analysis can evaluate the individual response to the clopidogrel loading dose prior to PCI and predict post-procedural major adverse cardiac events (MACE). In a study of Bonello et al., the optimal cut-off value of PRI assessed by VASP to exclude adverse events was 50% [40, 41].

VerifyNow P_2_Y_12_ test (Accumetrics, Inc., San Diego, CA) measures the agglutination of fibrinogen-coated beads by platelets stimulated by an agonist (ADP with prostaglandin E1) in citrated whole blood. The relevant thresholds are not clearly defined. Each assay records two results: P_2_Y_12_ reaction units (PRU) and percentage of inhibition. A good correlation has been established between the VerifyNow P_2_Y_12_ test and several other methods including the VASP assay [42].

Two blood samples for PRI and PRU testing will be drawn in Vacutainer tubes containing 3.8% trisodium citrate. The first sample will be collected at baseline following the randomization and then just before the index procedure. The analysis and the interpretation will be carried out in the Department of Cardiovascular Medicine of A. Gemelli Polyclinic or in the Grosseto Hospital according to the site of enrollment. The authors will store any residual blood sample for future research purposes.

For evaluation of the adenosine-induced effect of ticagrelor compared to clopidogrel, left-overs from the blood sampling will be utilized to measure the adenosine plasma concentration in the two groups together with ENT-1 expression and activity.

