## Abstract

**Background:**

Ticagrelor is a reversibly binding, direct-acting, oral, P_2_Y_12_ antagonist used for the prevention of atherothrombotic events in patients with coronary artery disease (CAD). Ticagrelor blocks adenosine reuptake through the inhibition of equilibrative nucleoside transporter 1 (ENT-1) on erythrocytes and platelets, thereby facilitating adenosine-induced physiological responses such as an increase in coronary blood flow velocity. Meanwhile, adenosine plays an important role in triggering ischemic preconditioning through the activation of the A1 receptor. Therefore, an increase in ticagrelor-enhanced adenosine bioavailability may confer beneficial effects through mechanisms related to preconditioning activation and improvement of coronary microvascular dysfunction.

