## Background

### Rationale

Ticagrelor is a reversibly binding, direct-acting, oral P_2_Y_12_ antagonist used for the prevention of atherothrombotic events in patients with acute coronary syndrome (ACS) [1]. It does not belong to thienopyridines; it is a carbocyclic nucleoside, representing a “first-in-class” cyclopentyl-triazolo-pyrimidine. In two phase II studies, dyspnea was noted to occur as a side effect to ticagrelor in a dose-dependent fashion, and in the PLATO study, a 6% absolute excess of dyspnea was observed in ticagrelor-treated patients compared with patients treated with clopidogrel [1]. In the ONSET/OFFSET study, dyspnea was more commonly associated with ticagrelor therapy in comparison with clopidogrel and placebo in patients with stable coronary artery disease (38.6%, 9.3%, and 8.3%, respectively) but was not associated with any adverse change in cardiac or pulmonary function [2]. Similar results were later confirmed in the population of patients with ACS [3].

The mechanisms for this side effect are largely unknown, although early data indicate that ticagrelor blocks adenosine reuptake through inhibition of ENT-1 transporter by erythrocytes [4], and intravenous adenosine infusion can cause transient dyspnea in the absence of bronchoconstriction [5]. Another mechanism potentially increasing adenosine levels by ticagrelor is reflected in adenosine triphosphate (ATP) release from erythrocytes [6]. Moreover, the biochemical comparison between ticagrelor and adenosine suggests their molecular similarity. Adenosine is a well-known key endogenous molecule that regulates tissue functions by activating four G-protein–coupled adenosine receptors: A1, A2A, A2B, and A3. Adenosine accumulates in the extracellular space in response to metabolic stress and cell damage, and elevations of adenosine are commonly encountered in conditions such as ischemia, hypoxia, inflammation, and trauma. Adenosine confers protective effects on the cell due to its anti-inflammatory, cardioprotective, cerebroprotective, antisclerotic, and antifibrotic properties, as well as by platelet inhibition and vasodilation [7].

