#### Ischemic preconditioning

During PCI, two sequential balloon inflations will be performed to measure preconditioning. Operators will measure the degree of ST-segment elevation by intracoronary ECG and by surface ECG during coronary balloon inflation.

Specifically, after passage of the guidewire through a target stenosis and then advancement of the balloon catheter across the stenosis, the intracoronary unipolar ECG from myocardium distal to the stenosis to be dilated will be obtained, connecting the proximal end of the guidewire as it exited from the balloon catheter. The unipolar intracoronary ECG will be filtered between 0.1 to 100 or 0.1 to 500 Hz and then displayed simultaneously with the standard surface leads being monitored. Surface and intracoronary ECGs will be recorded simultaneously and continuously during balloon inflation and deflation [43–45].

Moreover, angina score during coronary balloon inflation will be registered by using a Visual Analog Scale (VAS) on a scale of 0 (no pain) to 10 (most severe pain) [46]. For pharmacodynamic considerations, the Index PCI will be performed at 4 ± 1 h after ticagrelor or clopidogrel last dose.

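### Measuring plasma adenosine in left-over platelet-test blood can bias the arm comparison towards ticagrelor, because the drug's effect on adenosine uptake may continue in the tube

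*Protocol article*

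**What the plan says.** **The specimen.** Under Assessment of platelet reactivity, the comparison of adenosine between ticagrelor and clopidogrel rests on surplus blood: "left-overs from the blood sampling will be utilized to measure the adenosine plasma concentration in the two groups". ENT-1 expression and activity are to be measured from the same surplus.

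**The tubes.** The draws described in that section are these: "Two blood samples for PRI and PRU testing will be drawn in Vacutainer tubes containing 3.8% trisodium citrate". For VerifyNow the section says that platelets are "stimulated by an agonist (ADP with prostaglandin E1) in citrated whole blood". On timing it says: "The first sample will be collected at baseline following the randomization and then just before the index procedure". Table 1 fits this reading. At V1, the day of the index PCI, VASP and VerifyNow are the only blood tests listed. Blood count, chemistry and coagulation appear at V0 and V4.

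**The mechanism.** The Rationale says that "ticagrelor blocks adenosine reuptake through inhibition of ENT-1 transporter by erythrocytes", and the abstract's Background refers to "inhibition of equilibrative nucleoside transporter 1 (ENT-1) on erythrocytes and platelets". The Rationale adds: "Another mechanism potentially increasing adenosine levels by ticagrelor is reflected in adenosine triphosphate (ATP) release from erythrocytes". No such action is ascribed to clopidogrel.

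**Drug on board.** Under Ischemic preconditioning, "the Index PCI will be performed at 4 ± 1 h after ticagrelor or clopidogrel last dose", so a patient in the ticagrelor arm has recently taken the drug when the second sample is drawn.

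**The concern.** The measurement is meant to show whether adenosine in the patient is higher on ticagrelor. The blood chosen for it contains the cells that take up adenosine and, in one arm only, a drug that the protocol says blocks that uptake. Any time these cells spend in contact with plasma before separation can therefore change the analyte, and change it differently by arm.

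The direction is what makes this awkward. The error would look like the hypothesised finding, higher adenosine on ticagrelor. It is systematic, so more patients would not dilute it. The trial's stated goal is to explore pleiotropic effects as possible mechanisms, with adenosine as the proposed link, and this is the only planned measurement of adenosine concentration. If it cannot separate an effect in the patient from an effect in the tube, the step from drug to adenosine level stays undocumented, whatever the ST-segment and microvascular results show.

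**Working it through.** The plan gives no figure for this measurement, so there is none to reproduce. The check is a chain of statements, followed by an illustration of size.

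**Step 1: what the document fixes.** The specimen is surplus blood. The section describes only citrated platelet-test tubes, and V1 lists no other blood test. A blocker of uptake could hardly be put into those tubes at the draw without affecting the platelet assay they are drawn for.

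**Step 2: what follows.** Red cells and platelets carry ENT-1, and ticagrelor blocks it. If uptake goes on in the tube, it is slower where ticagrelor is present. Continued uptake is an inference from cells staying in contact with plasma; the document does not state it.

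**Step 3: formula.** Assume the same true concentration C in both arms and first-order loss in the tube. Let h be the number of uptake half-lives that pass before separation and f the fraction of uptake blocked by ticagrelor.

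- Clopidogrel tube: C × 2^(−h)
- Ticagrelor tube: C × 2^(−h(1−f))
- Spurious ratio, ticagrelor to clopidogrel: 2^(h×f)

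Neither h nor f is in the document. Both are assumptions, shown over a range:

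| h | f = 0.10 | f = 0.25 | f = 0.50 | f = 0.75 |
|---|---|---|---|---|
| 0.1 | 1.01 | 1.02 | 1.04 | 1.05 |
| 0.5 | 1.04 | 1.09 | 1.19 | 1.30 |
| 1 | 1.07 | 1.19 | 1.41 | 1.68 |
| 2 | 1.15 | 1.41 | 2.00 | 2.83 |
| 5 | 1.41 | 2.38 | 5.66 | 13.45 |

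One worked case: with h = 5 and f = 0.20, clopidogrel tubes keep 2^(−5) = 3.1% and ticagrelor tubes keep 2^(−4) = 6.3%, a ratio of 2^1 = 2.0.

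**Step 4: what needs no assumed value.** Within this model the ratio exceeds 1 whenever h > 0 and f > 0. With uptake stopped at the draw, h = 0 and the ratio is 2^0 = 1.00 for every f.

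**Step 5: does the baseline sample help?** Take the same h at both samples.

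- *Patients without ticagrelor in the baseline tube.* Both arms lose the factor 2^(−h) at baseline. At the second sample only the ticagrelor arm loses less. The ratio of changes is again 2^(h×f).
- *Patients on ticagrelor at entry, whom the inclusion criteria allow.* If f is the same at both samples, those who stay on ticagrelor show no spurious change. If those switched to clopidogrel have no ticagrelor effect left at the second sample, they show a spurious change of 2^(−h×f). The ratio between arms is 1 / 2^(−h×f) = 2^(h×f).

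Under these assumptions, adjusting for baseline leaves the artefact in place.

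**The case against.** The strongest objection is that this is laboratory detail. The article condenses a full protocol and refers to additional files that are not shown. Additives, chilling and time to separation normally sit there or in a laboratory manual, and their absence from an article is no fault. That is right as far as it goes, and unseen instructions could shorten the contact time. But the article does not just leave out handling detail. It chooses the specimen, as surplus from blood drawn for another purpose, and adenosine lost before the surplus is set aside cannot be recovered.

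Other parts of the objection stand and limit the point:

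- The sentence on left-overs does not name the citrate tube. That reading comes from the section and from Table 1 at V1. At V0 other bloods are drawn as well.
- Nothing says that plasma is separated only after the platelet tests are done. Surplus could be set aside and spun early.
- The size is assumed throughout. The model has loss only and no formation term, although the Rationale mentions ATP release from erythrocytes. It also stops being useful at long contact times. At h = 30 and f = 0.4 it gives 2^12 = 4096 with 2^(−30) of the adenosine left in clopidogrel tubes, which describes an unmeasurable analyte and not an arm effect.
- ENT-1 expression and activity are measured too, so adenosine concentration is not the trial's only mechanistic measurement.
- Plasma adenosine is in neither the primary nor the secondary endpoint list, and the study calls itself exploratory and a pilot.

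**Conclusion.** The point holds as a bias that the chosen specimen allows. With left-over platelet-test blood, a higher measured adenosine on ticagrelor could arise partly or wholly in the tube, and the plan as written gives no way to tell. This rests on three things: the left-overs are the citrated platelet-test samples, cells stay in contact with plasma for some time before separation, and uptake continues during that time. The differential action of ticagrelor is the protocol's own statement. The direction follows from these; the size does not. The range of 1.01 to 13.45 is illustrative and should not be cited as an estimate.

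Two stronger readings are tempting. A reader might infer that any adenosine difference found will be an artefact, perhaps a doubling. The document gives no half-life, blocking fraction or delay, so it supports only that such a difference can arise. A reader might also infer that the trial's main result is at risk. It is not: intracoronary ST-segment change, CFR, IMR, FFR and angina score do not depend on this blood sample. What is affected is the interpretation of one exploratory measure. The change is worth making because it is cheap; it is not a condition for the trial's validity.

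**What to change.** In Assessment of platelet reactivity, separate the adenosine measurement from the surplus blood:

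- At the venepunctures already planned, after randomization and just before the index procedure, draw one small dedicated tube for adenosine concentration. Stop uptake at the draw and separate the plasma at once. The laboratory should name the reagent and set a maximum time to separation.
- Keep left-over blood for the ENT-1 work, both expression and activity, as planned.
- For patients sampled only from left-overs, report adenosine concentrations descriptively by arm and draw no between-arm or mechanistic conclusion from them.

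Possible wording: *Adenosine concentration will be measured in a dedicated tube in which cellular uptake is stopped at the draw and from which plasma is separated immediately. Concentrations from residual platelet-test blood will be reported descriptively only.*

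The cost is one extra small tube with reagent and prompt centrifugation per sampling time, with no added visit or procedure. The new tube helps only patients still to be sampled. Recruitment began on 18 September 2018, is described as ongoing, and was expected to finish by the end of 2019, so that may be few. For the rest, the cost is a more restrained statement of what the stored samples can show.

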#### Ischemic preconditioning

During PCI, two sequential balloon inflations will be performed to measure preconditioning. Operators will measure the degree of ST-segment elevation by intracoronary ECG and by surface ECG during coronary balloon inflation.

Specifically, after passage of the guidewire through a target stenosis and then advancement of the balloon catheter across the stenosis, the intracoronary unipolar ECG from myocardium distal to the stenosis to be dilated will be obtained, connecting the proximal end of the guidewire as it exited from the balloon catheter. The unipolar intracoronary ECG will be filtered between 0.1 to 100 or 0.1 to 500 Hz and then displayed simultaneously with the standard surface leads being monitored. Surface and intracoronary ECGs will be recorded simultaneously and continuously during balloon inflation and deflation [43–45].

Moreover, angina score during coronary balloon inflation will be registered by using a Visual Analog Scale (VAS) on a scale of 0 (no pain) to 10 (most severe pain) [46]. For pharmacodynamic considerations, the Index PCI will be performed at 4 ± 1 h after ticagrelor or clopidogrel last dose.

#### Quantification of coronary microvascular resistance

CFR and IMR will be measured with an intracoronary pressure/temperature sensor-tipped guidewire (Radi pressure wire 4, Radi Medical Systems, Wilmington, Mass., USA), with an accuracy of 0.05 °C within a temperature range of 15–42 °C, to derive thermodilution curves. Previous experimental and human studies have demonstrated that the mean transit time (Tmn) of an intracoronary injection of saline at room temperature, derived from thermodilution curves, is inversely proportional to coronary flow [47–49]. Therefore, a given percent decrease in Tmn closely reflects a proportional percent increase in coronary blood flow. Three injections (3 mL each) of saline at room temperature will be performed, and the resting Tmn will be measured. An intravenous infusion of adenosine (Adenoscan, Sanofi Aventis S.p.A, Milan, Italy) at 140 μg/kg/min will be administered to induce a steady-state maximal hyperemia, followed by three further injections (3 mL) of room temperature saline to measure hyperemic Tmn.

Simultaneous measurements of mean aortic pressure (Pa, through the guiding catheter) and mean distal coronary pressure (Pd, by the pressure wire) will also be obtained in the resting and maximal hyperemic states. The following parameters will be calculated:
CFR will be calculated as the resting Tmn divided by the hyperemic Tmn [47, 48]IMR will be calculated as the distal coronary pressure at maximal hyperemia divided by the inverse of the hyperemic Tmn [50]BR (Baseline resistance index) will be calculated using the equation: BR = Pabase ×Tmnbase (Pdbase –Pw)/(Pabase –Pw) [51]RRR (resistive reserve ratio) will be calculated using the following equation: RRR = BR index / IMR [49, 50]

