**Methods:**

To determine whether ticagrelor can trigger ischemic preconditioning and influence microvascular function, we designed this prospective, open-label, pilot study that enrolled patients with stable multivessel CAD requiring staged, fractional flow reserve (FFR)-guided percutaneous coronary intervention (PCI). Participants will be randomized in 1:1 ratios either to ticagrelor (loading dose (LD) 180 mg, maintenance dose (MD) 90 mg bid) or to clopidogrel (LD 600 mg, MD 75 mg) from 3 to 1 days before the scheduled PCI. The PCI operators will be blinded to the randomization arm. The primary endpoint is the delta (difference) between ST segment elevations (in millimeters, mm) as assessed by intracoronary electrocardiogram (ECG) during the two-step sequential coronary balloon inflation in the culprit vessel. Secondary endpoints are 1) changes in coronary flow reserve (CFR), index of microvascular resistance (IMR), and FFR measured in the culprit vessel and reference vessel at the end of PCI, and 2) angina score during inflations. This study started in 2018 with the aim of enrolling 100 patients. Based on the rate of negative FFR up to 30% and a drop-out rate up to 10%, we expect to detect an absolute difference of 4 mm among the study arms in the mean change of ST elevation following repeated balloon inflations. All study procedures were reviewed and approved by the Ethical Committee of the Catholic University of Sacred Heart.

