## Abbreviations

ACS: Acute coronary syndrome
AE: Adverse events
AIFA: Agenzia Italiana del Farmaco
ANOVA: Analysis of variance
BP: Blood pressure
BR: Baseline resistance index
CAD: Coronary artery disease
CBFV: Coronary blood flow velocity
CFR: Coronary flow reserve
CFVR: Coronary flow reserve velocity
CTC: Clinical Trial Center S.p.A.
DAPT: Dual antiplatelet therapy
EC: Ethics committee
eCRF: Electronic case report form
EMA: European Medicines Agency
FFR: Fractional flow reserve
FPG: Fondazione Policlinico Universitario A. Gemelli
HR: Heart rate
IC: Informed consent
ICH: International Conference on Harmonization
IMR: Index of microvascular resistance
MACE: Major adverse cardiac events
NSTEMI: Non-ST-elevation Acute Coronary Syndromes
Pa: Aortic pressure
PCI: Percutaneous coronary intervention
Pd: Distal coronary pressure
PRI: Platelet reactivity index
PRU: P2Y_12_ reaction units
*Pw*: Wedge pressure
RISK: Reperfusion injury salvage kinases
RRR: Resistive reserve ratio
SAE: Serious adverse event
SD: Standard deviation
SUSAR: Suspected unexpected serious adverse reactions
T_mn_: Transit time
VASP: Vasodilator-stimulated phosphoprotein

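### RRR divides a wedge-corrected resting resistance by an uncorrected hyperaemic IMR; the two terms should share one definition (small effect, non-endpoint index)

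*Protocol article*

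**What the plan says.** The section on quantification of coronary microvascular resistance gives three linked definitions.

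- Resting index: "BR = Pabase ×Tmnbase (Pdbase –Pw)/(Pabase –Pw"), a form that contains Pw. The abbreviation list expands Pw as "Wedge pressure".
- Hyperaemic index: "IMR will be calculated as the distal coronary pressure at maximal hyperemia divided by the inverse of the hyperemic Tmn". Dividing by the inverse of Tmn is multiplying by Tmn, so IMR = Pd × Tmn at hyperaemia, without Pw.
- Reserve ratio: "RRR = BR index / IMR".

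The pressures to be obtained, at rest and at hyperaemia, are described as "Simultaneous measurements of mean aortic pressure (Pa, through the guiding catheter) and mean distal coronary pressure (Pd, by the pressure wire"). Pw is not listed there.

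The secondary endpoints under Study endpoints are CFR, IMR and FFR in the index vessel at the end of PCI, and the angina score. BR and RRR are not among them. The Statistical analysis section does say that all variables will be summarised by arm and visit, so RRR can be expected in the report.

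**The concern.** A reserve ratio is meant to compare one quantity in two states. Here the quantity changes definition between rest and hyperaemia, so the ratio mixes the physiological change with the change of formula.

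The wedge correction grows with the pressure drop across the vessel. It is therefore smallest at rest, where the article applies it, and largest at hyperaemia, where the article leaves it out. The result is too low against either consistent definition.

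What is at stake is the meaning of one exploratory index. RRR values from this trial would not match a ratio built on either convention, and the discrepancy would vary from patient to patient with the residual gradient and with Pw.

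**Working it through.** The article prints no RRR value, so there is no figure to reproduce. The check is algebra, followed by an illustration on assumed pressures.

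**Formulas (from the article).**

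- Corrected resistance: Pa × Tmn × (Pd − Pw)/(Pa − Pw)
- Uncorrected resistance: Pd × Tmn
- Their ratio: f = Pa(Pd − Pw) / [Pd(Pa − Pw)]

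Because Pa(Pd − Pw)/(Pa − Pw) = Pd − Pw(Pa − Pd)/(Pa − Pw), f equals 1 only if Pw = 0 or Pd = Pa. With Pw > 0 and Pd < Pa it is below 1, and it falls as the gradient widens. Tmn cancels from f.

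**What the printed RRR is compared with.**

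- Printed RRR / both-uncorrected RRR = f at rest.
- Printed RRR / both-corrected RRR = f at hyperaemia.

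**Assumed inputs (none is in the article).** Pa 90 mmHg; resting Pd 88 mmHg; hyperaemic Pd/Pa 0.92 at the end of PCI, so Pd = 82.8 mmHg; Pw 20 mmHg, with a range of 10 to 25.

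At Pw 20:

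- Rest: 90 × 68/70 = 87.43, and 87.43/88 = 0.9935. RRR is about 0.6% low against both-uncorrected.
- Hyperaemia: 90 × 62.8/70 = 80.74, and 80.74/82.8 = 0.9752. RRR is about 2.5% low against both-corrected.

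| Pw (mmHg) | f at rest | Against both-uncorrected | f at hyperaemia | Against both-corrected |
|---|---|---|---|---|
| 10 | 0.9972 | −0.3% | 0.9891 | −1.1% |
| 20 | 0.9935 | −0.6% | 0.9752 | −2.5% |
| 25 | 0.9913 | −0.9% | 0.9666 | −3.3% |

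**Sensitivity to the residual gradient.** With resting Pa 95 and hyperaemic Pa 90 mmHg, resting Pd/Pa 0.96, hyperaemic Pd/Pa 0.88 and Pw 10, 20 or 30, the printed RRR is 1.7%, 3.9% or 6.8% below the both-corrected ratio and 0.5%, 1.1% or 1.9% below the both-uncorrected one. With no gradient it agrees with both.

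**How the two consistent ratios differ.** At Pw 20 and hyperaemic Pd/Pa 0.92, the both-uncorrected ratio is 0.9752/0.9935 = 0.982 of the both-corrected one, about 1.8% lower. Most of the 2.5% therefore reflects the choice to leave IMR uncorrected. The part due to mixing definitions is about 0.6%.

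**The case against.** The strongest reply is that this hardly matters. RRR is not an endpoint, and no listed endpoint uses the mixed formula. The listed physiology is taken at the end of PCI, when little gradient should remain, and patients with visible collaterals are excluded, which favours a low Pw. Both arms use the same formula, so a common shortfall largely cancels. Even if residual hyperaemic Pd/Pa were 0.88 in one arm and 0.92 in the other, the shortfalls at Pw 20 would be 3.9% and 2.5%, a difference of 1.4 percentage points. All of this stands, and it sets the weight of the point.

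It can also be said that the formulas carry citations that are not at hand, so whether the mixed form follows a published index cannot be judged here. That is fair. The inconsistency is nevertheless visible in the printed definitions alone.

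A reader might go further and infer that RRR cannot be calculated, since Pw is not among the listed pressures. The article does not support that for the index vessel. Pw is in the equation and in the abbreviation list, the vessel is occluded by two balloon inflations, and a condensed article commonly leaves such a recording step to the full protocol. For a reference vessel the inference rests on the abstract alone ("measured in the culprit vessel and reference vessel at the end of PCI"). That sentence concerns CFR, IMR and FFR, and nothing says that BR or RRR will be computed there.

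**Conclusion.** The inconsistency is real and minor. RRR as printed is below a both-corrected ratio whenever Pw > 0 and a hyperaemic gradient remains, and below a both-uncorrected ratio whenever Pw > 0 and a resting gradient remains. The direction follows from the algebra; the size depends on the assumed pressures. At the end of PCI it is about 0.6% against the uncorrected convention and about 2.5% (1.1% to 3.3% for Pw 10 to 25) against the corrected one.

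Two stronger readings should not be drawn.

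- Applying the algebra to an untreated lesion gives larger figures: at FFR 0.70, with the same Pa and Pw, RRR is about 12% low and IMR about 14% above its corrected form. The endpoint section takes these measurements at the end of PCI, so that is not the state compared. Those figures also come almost wholly from leaving IMR uncorrected, not from mixing definitions.
- A reader might infer that part of any improvement in IMR would only be relief of the stenosis. The article defines IMR in one consistent way and schedules no pre-PCI IMR in the text shown. The abstract's mention of changes is tied to the end of PCI, and relief of the stenosis would occur in both randomised arms.

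**What to change.** Use one resistance definition in both states.

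- Simplest: RRR = (resting Pd × resting Tmn)/(hyperaemic Pd × hyperaemic Tmn). This keeps IMR as defined, uses only pressures and transit times already recorded, needs no Pw, and also works in any vessel that is not occluded.
- If the wedge-corrected form is preferred: apply it to both terms, in the index vessel only, and list Pw among the recorded pressures.

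The choice should be written down before the data are analysed. The first option costs one line in the formula list and no new data; the second adds one data field.
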